# The Child Healthcare at MATER Pediatric Study (CHAMPS): a 2-arm cluster randomized control trial of group well child care for mothers in treatment for opioid use disorder and their children

**DOI:** 10.1186/s13063-023-07357-2

**Published:** 2023-05-17

**Keywords:** Group well child care, Opioid use disorder

## Abstract

**Background:**

Studies suggest that group-based well child care—a shared medical appointment where families come together as a group to receive pediatric primary care—increases patient-reported satisfaction and adherence to recommended care. Evidence supporting the use of group well child care for mothers with opioid use disorder, however, is lacking. The overall objective of the Child Healthcare at MATER Pediatric Study (CHAMPS) trial is to evaluate a group model of well child care for mothers with opioid use disorder and their children.

**Methods:**

CHAMPS is a single-site 2-arm cluster randomized controlled trial. A total of 108 mother–child dyads will be enrolled into the study. Twenty-six clusters of approximately 4 mother-infant dyads each will be randomized 1:1 to one of two study arms (intervention or control). Clustering will be based on child’s month of birth. In the intervention arm, group well child care will be provided on-site at a maternal substance use disorder treatment program. Mother–child dyads in the control arm will receive individual well child care from one nearby pediatric primary care clinic. Dyads in both study arms will be followed prospectively for 18 months, and data will be compared between the two study arms. Primary outcomes include well child care quality and utilization, child health knowledge, and parenting quality.

**Discussion:**

The CHAMPS trial will provide evidence to determine if a group well child care offered on-site at an opioid treatment program for pregnant and parenting women is beneficial over individual well child care for families impacted by maternal opioid use disorder.

**Trial registration:**

ClinicalTrials.gov identifier: NCT05488379. Registered on Aug. 04, 2022.

## Administrative information

Note: the numbers in curly brackets in this protocol refer to SPIRIT checklist item numbers. The order of the items has been modified to group similar items see http://www.equator-network.org/reporting-guidelines/spirit-2013-statement-defining-standard-protocol-items-for-clinical-trials/).

## Introduction

### Background and rationale {6a}

In the past two decades, the rate of opioid use disorder (OUD) among pregnant women has more than quadrupled, constituting a US public health crisis [1–3]. Perinatal OUD presents a unique set of healthcare challenges for affected mothers and their children across a continuum of care. For this population, multiple clinical and psychosocial risk factors contribute to increased rates of pregnancy complications, newborn morbidity, and childhood developmental and health concerns. Although most research on perinatal OUD has focused on pregnancy and birth hospitalization care, fewer studies have focused on pediatric primary care after discharge from the hospital, when ongoing risks associated with OUD may include a myriad of factors including fear of stigma, low health literacy, maladaptive parenting behaviors, and economic and social barriers to seeking healthcare.

Addressing social and emotional determinants of health is a core focus of pediatric primary care clinicians, particularly in the context of well child care (WCC) visits. WCC visits, which occur at age-specific intervals defined by the American Academy of Pediatrics, emphasize anticipatory guidance, psychosocial screening, connection to community resources, and assessments of child growth, health, development, and behavior. There is evidence that WCC could be improved for children impacted by maternal OUD, who often experience multiple clinical and psychosocial concerns in infancy and early childhood such feeding difficulties, hepatitis C exposure, and developmental delays [4]. Despite these concerns, low attendance to WCC for this patient population has been reported [5], and mothers with OUD have described traditional WCC visits in the pediatric primary care setting as limited in time and resources to comprehensively address their questions and needs [6, 7]. Lack of time and resources to comprehensively address care needs of mothers with OUD and their children has also been reported by primary care pediatricians [8]. There is an urgent need for research to enhance the effectiveness, perceived value, and quality of pediatric primary care for this growing and underserved population.

One promising intervention for mothers in treatment for OUD and their children is group WCC, in which multiple mother–child dyads receive pediatric care together. Group WCC visits encourage increased breadth and depth of discussion, peer-to-peer support, and greater emphasis on self-care and behavior change. In addition to standard WCC topics focused on child health and development, the group WCC visit format places emphasis on maternal wellness including nutrition and exercise, family planning, stress reduction, and interpersonal relationships. Available research suggests this intervention increases patient-reported satisfaction and adherence to recommended care [9–13]. However, evidence supporting the use of group WCC for mothers with OUD is lacking.

### Objectives {7}

The overall objective of this trial is to evaluate a group model of WCC for mothers with OUD and their children.

### Trial design {8}

This is a single-site cluster randomized controlled trial. One hundred eight pregnant and parenting women receiving treatment for OUD from one single opioid treatment program will be enrolled into the study. Twenty-six consecutive clusters—based on the one-month birth intervals of participants’ infants—of ~ 4 dyads will be randomized in a 1:1 ratio to one of two study arms. Thirteen clusters will be randomized to individual WCC (control group), and 13 birth clusters will be randomized to group WCC (intervention arm), with concealment of randomization from participants until after they have completed their initial enrollment study visit, or, for those who are pregnant at time of enrollment, immediately following delivery. Randomization by birth month was selected to ensure a close age range among infants receiving group WCC together in the intervention arm. Blocking or stratification was not used in the randomization. Dyads in both study arms will be followed prospectively for 18 months, and data will be compared between the two study arms. Primary outcomes include well child care quality and utilization, child health knowledge, and parenting quality. We hypothesize that at the end of the study period, participants in the intervention arm will have increased WCC engagement, knowledge about parenting, and maternal responsiveness compared to participants in the control arm.

## Methods: participants, interventions, and outcomes

### Study setting {9}

This trial is conducted within a single, urban substance use disorder (SUD) treatment center affiliated with a university and university health system. The treatment center includes a licensed outpatient opioid treatment program and a residential treatment program, both of which serve pregnant and/or parenting women exclusively. At both outpatient and residential levels of care, all patients receive comprehensive wraparound services, including methadone and buprenorphine as medications for OUD, psychiatric medications and psychotherapy, cognitive behavioral therapy and mindfulness-based therapy for substance use disorder in individual, family, and group formats, case management, medical care coordination, peer recovery support, mindfulness-based parenting psychoeducation, and various other services especially needed by the population of pregnant and/or parenting women with SUDs. At the residential level of care, women live with their children at the facility and receive the majority of programming at the facility for an average of 6 months. Upon completion of residential treatment, the majority of patients continue their SUD treatment at the outpatient facility. Patients are welcome to participate in the outpatient program for as long as they desire, and the average length of outpatient treatment is 3–4 years. Across both programs, the treatment center serves approximately 250 women each year.

### Eligibility criteria {3}

Inclusion criteria for screening for and consent into the trial are as follows: (1) 18 years or older, (2) at least 28 weeks pregnant or parenting a child less than 12 months of age, (3) receiving treatment for OUD from the recruitment opioid treatment program, (4) ability to read and speak English, (5) plans to parent infant after delivery (if pregnant), (6) intent to seek pediatric care within the affiliated health system, and (7) intent to remain in the local area for the next 2 years. Exclusion criteria include (1) inability to speak English, (2) plans to move outside of the local area in the next 2 years, (3) plans to not parent infant after delivery, and (4) plans to seek pediatric care outside of the affiliated health system.

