### Criteria for discontinuing or modifying allocated interventions {11b}

Patients can leave the study at any time for any reason if they wish to do so without any consequences. Following a live birth, participants will remain eligible to continue in the study unless the mother and/or infant experiences the following: gestational age at time of delivery less than or equal to 32 weeks or illness or clinical complication warranting prolonged hospitalization after delivery. Even when a participant randomized to the intervention does not receive the intervention, we will attempt to complete the follow-up data collection to ensure a complete dataset.

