#### Primary outcomes

*WCC engagement*: measured as both utilization and experience of WCC.*WCC utilization*: The total number of age-appropriate WCC visits during the 18-month study period will be abstracted from the pediatric electronic medical record (EMR). Adequacy of WCC during this time will be dichotomized as “adequate” (completes the recommended number of WCC visits) or “inadequate” (does not complete the recommended number of WCC visits). This definition is adapted from the Health Plan Employer Data and Information Set (HEDIS) measure for WCC [20]. The mean number of age-appropriate WCC visits during the 18-month study period and the proportion of participants with adequate WCC over the 18-month study period will be compared between the 2 study arms.*WCC experience*: The *Promoting Healthy Development Survey* (PHDS) [21], a 43-item standardized, validated parent survey designed to measure the quality and content of care for children 3–48 months, is completed by participants at the 6-, 12-, and 18-month follow-up assessment visits. The PHDS will be used to evaluate participants’ perceptions of their child’s WCC, including (1) anticipatory guidance—whether the mother received age-appropriate guidance; (2) developmental surveillance—whether the mother was asked about concerns about her child’s learning, development, or behavior, and if concerns were addressed; (3) family-centeredness—whether the mother felt her perspective was heard and valued; (4) family risk assessment—whether the mother was asked about issues in the family (e.g., substance use, emotional support); and (5) helpfulness of care—how helpful the care provided was in specific aspects of parenting (e.g., understanding child behavior). Multiple survey items are used to calculate a score for each component of care evaluated and these composite measures have been previously tested for internal consistency. The mean score for each component of care at each time point will be compared between the 2 study arms.*Parenting knowledge*: The medical literature was reviewed for previously validated questions used to assess parental knowledge about the care and development of intrauterine opioid-exposed infants; no prior questions were identified. Therefore, a survey instrument includes investigator-developed questions specific to this area, (e.g., “Breastfeeding increases the chance your baby will have opioid withdrawal symptoms: Agree/Disagree/Not Sure”), as well as questions from the Knowledge of Infant Development Inventory (KIDI) [22]. The KIDI is a widely used measure of parenting knowledge designed as a diagnostic tool for high-risk parents. The KIDI consists of 58 items grouped into four categories (norms and milestones, principles, parenting, and health and safety) that tests mothers’ knowledge of children’s development and parenting of children from birth through 36 months of age. Items are measured on a 5-point Likert scale with higher scores indicating correct knowledge and developmentally appropriate expectations. In addition to a total knowledge score calculated by summing the number of correct items and calculating an average, four KIDI subscale scores and a knowledge of infant opioid exposure score will also be generated. The total and subscale score at 18 months will be compared between the 2 study arms. The mean change in scores from baseline to 18 months follow-up will be compared between the two study arms.*Maternal-child interaction quality*: This is directly assessed using video-recorded mother/child free play at an 18-month follow-up assessment visit. Interactions are coded by certified scorers using the Keys to Interactive Parenting Scale (KIPS) [23]. KIPS assesses 12 parenting behaviors using quality ratings ranging from 1 to 5 within three domains sub-scale domains: building relationships, promoting learning engagement in language experiences, and supporting confidence. A total score is generated by summing the 12 items and calculating an average to indicate low, moderate, and high-quality parenting behavior. The total and subscale score at 18 months will be compared between the 2 study arms.

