### Participant timeline {13}

### Sample size {14}

Assuming 150 births in the opioid treatment program over an 18-month recruitment period, > 90% rate of maternal legal guardianship at birth, 80% study participation rate, and equivalent group allocation (50%), we expect to enroll 108 participants (n = 54 per study arm) during the project period. A sample size of 54 per study arm will produce a two-sided 95% CI with a distance from the standardized difference in means between two arms to the limits that are equal to 0.38. Additionally, with a sample size of 54 per study arm, a two-sided test for the time-averaged difference between two means in a repeated measures design with a significance level of 0.05 will have 80% power to detect a standardized difference in means of 0.43 in a design with 4 repeated-measurements taken over the 18-month period and with between level correlations of 0.5. A sample size of 54 per study arm will give us 80% power to detect a standardized difference in means of 0.54 (effect size) between two arms using a two-sided two-sample t-test with a significance level of 0.05. Of note, we were unable to find reported data about the cluster effect of different birth months. However, we expect only a negligible cluster effect for birth-month, and so assumed no to negligible intra-cluster correlation coefficient (ICC; 0 to 0.05) to perform the power calculations, which is almost equivalent to performing simple random sampling. However, we preferred the design of cluster random sampling to simple random sampling to account for the effect of birth-month if there is any.

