
### Plans to promote participant retention and complete follow-up {18b}

Multiple strategies are used to retain participants over the duration of the study, including (1) providing reminders (e.g., calls, texts) before study data collection visits; (2) limiting participant burden by scheduling data collection study visits when participants are already attending the SUD treatment center; (3) using limited release of medical information forms for EMR abstraction; (4) providing incentives after completion of data collection visits; (5) paying for car ride services (e.g., Uber) and providing parking vouchers to nearby parking garages so participants can park during study visits; (6) collecting contact information of friends and family members who are likely to know the location of subjects should they be temporarily out of contact; and (7) sharing information about the study with staff and providers across hospital departments (e.g., Neonatology, General Pediatrics, Ob/Gyn). In addition, our approach to analyzing the data will allow us to include subjects in analyses who provide partial data due to premature study dropout. Comparisons between study subjects who are retained and who drop out will be conducted to determine biases and non-random patterns of study attrition.

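### The primary utilization outcome is a two-class count from the pediatric EMR, so as written a child who moves to a practice outside the affiliated system is classed as inadequate even if visits were attended elsewhere

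*Protocol article*

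**What the plan says.** **Eligibility criteria {3}.** Use of the affiliated system and staying in the area are both tested as intentions at enrollment: "intent to seek pediatric care within the affiliated health system" and "intent to remain in the local area for the next 2 years". Enrollment is open to women "at least 28 weeks pregnant or parenting a child less than 12 months of age", so for some the statement is made before the child is born.

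**Primary outcomes.** WCC utilization is the number of age-appropriate visits found in the pediatric EMR over the 18-month study period. It is then split into two classes. A child is adequate if the recommended number was completed, and inadequate if the child "does not complete the recommended number of WCC visits". Both the mean count and the proportion adequate are compared between arms. There is no class for a child who has left the system or whose care is unknown.

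**Criteria for discontinuing or modifying allocated interventions {11b}.** The listed reasons for losing eligibility after birth are clinical (early delivery, prolonged hospitalization). A change of practice is not among them.

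**Plans to promote participant retention and complete follow-up {18b}.** One retention measure is "using limited release of medical information forms for EMR abstraction". The article does not say whether these forms reach outside practices, or whether outside visits count toward the outcome.

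**Methods in analysis to handle protocol non-adherence and missing data {20c}.** Missingness will be investigated and imputation considered, in general terms.

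**The concern.** An EMR count is never blank. A child seen elsewhere does not show up as missing; the child simply has fewer recorded visits. The general missing-data provision therefore has nothing to act on unless someone has recorded that the child left. The outcome cannot separate care not received from care not observed, and it is a primary outcome.

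Two consequences follow. If leaving is similar in both arms, adequacy is understated and a true difference shrinks. If leaving differs between arms, a difference can appear where there is none. Departure dates and outside visits that are not collected during follow-up may be impossible to recover at analysis, so this belongs to data collection and outcome definition as much as to the analysis plan.

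**Working it through.** **The plan's own figures.** In Sample size {14}, 150 × 0.90 × 0.80 = 108, or 54 per arm. With 54 per arm, a standardized difference of 0.54 and two-sided 0.05, power is 80.1% (79.4% from the noncentral t distribution). These figures reproduce and are not in dispute.

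**One child.** From 1 to 18 months the intervention schedule lists visits at 1, 2, 4, 6, 9, 12, 15 and 18 months: 8 visits. Suppose a child attends all 8 but changes to an outside practice after the 9-month visit, and those records are not obtained. The EMR then shows 5 of 8, and the child is inadequate under the stated rule. (This takes these 8 visits as the recommended number and leaves out the newborn visit.) The per-protocol set in Methods for additional analyses {20b} requires 75% of recommended sessions, or 0.75 × 8 = 6. If it is counted from the same record, this child is lost there too.

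**Formula for a group.** Let q be true adequacy and m the share of truly adequate children whose outside visits are not seen. Then observed adequacy = q × (1 − m). The documents give neither q nor m, so all values below are assumptions. Power and rejection rates use 54 per arm, a two-sided 0.05 test of two proportions, and ignore clustering.

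*Equal leaving with a true effect*, 50% against 76% (80.8% power if every visit is seen):

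| m in both arms | Observed adequacy | Difference | Power |
|---|---|---|---|
| 5% | 47.5% vs 72.2% | 24.7 points | 75% |
| 10% | 45.0% vs 68.4% | 23.4 points | 69% |
| 20% | 40.0% vs 60.8% | 20.8 points | 58% |
| 30% | 35.0% vs 53.2% | 18.2 points | 48% |

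*Unequal leaving with no true effect*, q = 60% in both arms. The control arm is given the larger loss for illustration only; reversing the arms reverses the sign.

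| m, intervention vs control | False difference | Rejection rate |
|---|---|---|
| 5% vs 10% | 0.60 × 0.05 = 3 points | 6.1% |
| 5% vs 15% | 57% − 51% = 6 points | 9.5% |
| 5% vs 20% | 0.60 × 0.15 = 9 points | 15.4% |
| 10% vs 30% | 0.60 × 0.20 = 12 points | 23.7% |

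For 5% vs 15%, true adequacy of 50% or 70% gives 5 or 7 points.

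**Scale.** The 6-point case is about 3 children (0.06 × 54 = 3.2). Its unclustered standard error is √[(0.57 × 0.43 + 0.51 × 0.49)/54] = 9.6 points, so the bias is about 0.6 standard errors.

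**The case against.** No sentence in the article says that a child who leaves the system is scored inadequate. The release forms might be used for outside records, the investigators state that "we will attempt to complete the follow-up data collection to ensure a complete dataset", and a fuller protocol or analysis plan may settle the coding. This stands to the extent that the scoring is a consequence of applying the definition literally, not a separately stated rule. It does not remove the point, because the published definition already places every child in one of two classes, and the provisions cited neither add outside visits nor flag a departure.

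A reader might also infer three stronger things that the documents do not support:

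- *That group care is favored.* Intervention visits take place at the treatment program and control visits at a separate office, so more control families might seem likely to leave. But the control practice is hospital-owned and five blocks away, and a nurse coordinator follows up missed visits. Intervention families also use the affiliated office for newborn visits and after missed groups, and both arms are screened on the same intention. No leaving rate is given for either arm.
- *That loss of custody scores a child as missing care.* The record is the child's. A child brought to the affiliated practice by another carer still has visits in it. Custody matters for this outcome only if it also takes the child out of the system. Women who enroll after delivery must already be parenting, so eligibility does not rest on intention alone in that respect.
- *That the plan expects up to 10% of participants to lack guardianship.* The "> 90% rate of maternal legal guardianship at birth" is a recruitment-yield factor applied before the 108 is reached, and says nothing about enrolled dyads during follow-up.

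Finally, counting only care recorded in the affiliated system is a defensible choice. Treating all leavers as unknown in the main analysis would have its own weakness: if leaving goes with disengagement, it is an informative exclusion from an intention-to-treat comparison. That objection stands and shapes the fix.

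**Conclusion.** The point holds for a change of practice. The definition combines an EMR-only count with two exhaustive classes, while remaining in that EMR is secured only by intent at enrollment. A child who moves outside the system, and whose records are not obtained, is classed as inadequate regardless of attendance.

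The effect on the comparison cannot be sized from the documents. In the illustrations, an equal 10% loss reduces power from about 81% to 69%, and 5% against 15% leaving produces a false 6-point difference. Both assume that children who leave would have been adequate as often as the others, and that none of their outside visits are seen; if attendance falls after a move, fewer are misclassified. The arithmetic shows that modest leaving would matter. It does not show that such leaving will occur, or which arm it would favor. The change is worth making because it is cheap and much harder to make after follow-up has ended.

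**What to change.** 1. At the existing 6-, 12- and 18-month visits, record whether the child's pediatric care has left the affiliated system, and the date.
2. State in the outcome definition that WCC visits at outside practices count toward the total and toward adequacy. Obtain them through the release forms already in use, extended to outside practices if their scope does not cover them.
3. Where outside records cannot be obtained, report adequacy both ways: with those children scored inadequate, and with their visits due ended at the departure date or their adequacy treated as missing.
4. Report the number leaving, by arm.

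The cost is a few questions at visits that already take place, some record requests, and one added analysis. The analysis that treats leavers as missing may exclude children informatively, so it should accompany the count that scores them inadequate and not replace it.
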